**Fig. 2 Fig2:**
[figure not shown]
Schedule of enrolment, interventions, and assessments

After assessment, the research PT visits the participant’s home to install the equipment and finish training. The games, safety considerations and follow-up procedures are reviewed with the participant and his or her study partner. Participants in both groups are instructed to perform their exercises five times a week for 6 weeks. VRT sessions are designed to run for approximately 30 min of activity time and participants in the iPad group are asked to use it for at least 30 min a day. This amount of additional training (15 h) has been shown to produce a significant improvement in activities of daily living post stroke [38]. The study partner must be in the home of the participant while he or she is doing VRT.

All participants are contacted by the research PT via telephone or email twice a week for the first week and at least once a week for the following 5 weeks to offer encouragement, suggest modifications to the games and identify any safety issues or technical problems. Participants are also invited to contact the research PT as needed. For those in the experimental group, the research PT monitors the compliance and success rate of VRT at least once a week using the remote access feature of the VRT system, and can modify the games if necessary.

Participants in both groups are provided with a logbook in which to record technical issues with the VR equipment, thoughts on how the games are going and if progression was required, safety concerns and adverse events and changes to the exercise environment. Those in the control group must also record the time spent on the iPad apps each day and which apps are used. Participants are encouraged to do as many activities of daily living (ADL) and instrumental ADLs as they wish, including walking, participation in exercise groups and therapy. Throughout training and during the intervention, every attempt is made to equalize contact time with the research personnel between the two groups.

After the 6-week exercise protocol is completed, participants return to Élisabeth Bruyère Hospital for their post-intervention assessment (1½ h). During the post-intervention assessment, the physical outcome measures and community integration questionnaires are repeated, the PACES is administered and a semi-structured interview takes place with a second RA in which participants and their study partners are asked several questions about their experience with VRT (Additional file 2: Figure S2). Once outcome measures are completed the research PT visits the participant’s home for a second time to remove the equipment.

### Data management and analysis

All data will be coded with a participant number; the code breaker will be kept in a different area on the computer server in a password-protected file. A database will be kept with demographic information (age, sex, details of stroke, medical history etc.) and the results of the physical outcome measures and questionnaires. Data on recruitment, retention, number of exercise sessions undertaken in 6 weeks and the number of minutes for each session will be included. Major and minor adverse effects will be recorded and ancillary care will be provided if required.

The pre-intervention and post-intervention scores for the BBS, TUG, FTSST, CB&M, SIS, RNLI and PACES will be reported as mean (95% confidence intervals). Missing data will be handled using complete case analysis. Each scale (except the PACES, which is assessed post-intervention only) will be compared using mixed-methods analysis of variance (ANOVA) (within-group factor, time; between-group factor, group; interaction, time x group). For quiet stance and limits of stability in sitting and standing, an ellipse encompassing 95% of the center of pressure data points will be computed. The area, anteroposterior and mediolateral dimensions of this ellipse will be determined. Results will be compared over time using mixed-methods ANOVA as aforementioned. Linear regression will be used to analyze what proportion of the results of the physical outcome measures is explained by motivation to undertake physical activity (assessed with the Motivation for Physical Activity Questionnaire and the PACES).

Recordings from the interviews will be transcribed. Qualitative data from the transcribed interviews, log books and records of contacts with the participants will be grouped, organized and classified into categories or themes [39, 40]. The categories will be examined to answer primary research objectives 2, 3, 4 and 5, and secondary objective 1 on the enjoyment of VRT, safety, difficulties with the technology or exercises and perceived effectiveness. The datasets created during this study will be available from the corresponding author on reasonable request.

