**Trial Registration:**

ClinicalTrials.gov, NCT03261713. Registered on 21 August 2017. Registration amended on 1 June 2018 to decrease enrollment from 40 to 20 due to a cut in study funding and difficulty recruiting participants.

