### Sample size and recruitment

No sample size calculation was performed as this is a feasibility trial. The sample size of two groups of 20 is based on available time and recruitment expectations and funding level. It is expected that having 20 participants in the VRT arm of the study will be enough to discern the feasibility of home-based VRT. It is deemed reasonable that 40 out of the estimated 375 stroke rehabilitation inpatients and the 375–450 patients who attend outpatient stroke rehabilitation over 18 months will be eligible and interested in the study. Members of the clinical care team will be made aware of the study through their clinical manager and attendance at team meetings. The study will be stopped prematurely if serious adverse effects occur.

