### Randomization, allocation and blinding

Participants are enrolled by the RA. A computer-based randomization system (Sealed Envelope, London, UK) is used to allocate participants in a 1:1 ratio to either experimental or control groups, using permuted blocks while maintaining concealment. The research physiotherapist (PT) accesses the system immediately after the participant is enrolled; the allocation is provided immediately. The only person blinded to treatment allocation is the RA, who performs the outcome measures. The research PT is blinded to the results of the outcome measures. If the participant is undergoing rehabilitation during the study period (for example, outpatient or community-based rehabilitation), the rehabilitation professional is informed of their patient’s participation in the study, to ensure that the home-based exercise is compatible with the participant’s therapy. The PT will reveal a participant’s allocation in the case of serious adverse effects.

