### Outcome measures

To address each primary objective as numbered, the following outcome measures are used:The number of participants recruited over 18 months will be determined relative to the number who met the study participation criteria and the number who were approached by the clinical staff and the RA. The inability to recruit at least 30 participants will require the researchers to alter recruitment procedures for a definitive RCT.Ability to comply with the research protocol will be assessed through notes taken by the research PT and comments provided by the participant and study partner in the log book, on the phone and at the interview. If a majority of participants perform less than 450 min of VRT over the 6 weeks (900 min is the requirement of the protocol), the use of VRT as a motivation to encourage people to exercise post stroke will be reconsidered and reasons why will be discerned. Retention of participants will be measured and a loss of more than 25% will suggest that changes should be made to the protocol.The presence of adverse effects will be recorded from telephone conversations with the participant and through the log book. The occurrence of major adverse effects (e.g. falls with serious injuries) would suggest that home-based VRT, as used in this protocol, is too risky to continue.Ability to use VRT in the home will also be assessed through comments written in the log book or made by the participants during VRT installation and follow-up phone calls and in the interview. Use and progression of the VRT program will be monitored asynchronously by the research PT. Poor learning would be implicated if no progression is observed. Also, expressions of frustration or confusion with the games will indicate poor ability to do VRT.Acceptability of VRT will also be assessed using information gleaned from the log books and follow-up phone calls and from the Physical Activity Enjoyment Scale, which rates (from 1 to 7) 18 statements of one’s feelings about physical activity (PACES) [20], administered at the post hoc assessment only.Costs related to the VRT equipment/licences, travel and salaries will be calculated, in order to prepare a budget for a definitive RCT.

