The following outcomes will be used to address each secondary objective.The first secondary objective (feasibility and acceptance of a battery of outcome measures) will be assessed by recording the completion of 11 outcome measures, including physical outcomes (5 tests), questionnaires (4 in total), a log book and a semi-structured interview. The inability of all participants to complete the outcome measures, within a reasonable time frame (2 h) will result in re-thinking the use of each measure in a definitive RCT.The potential for VRT to maintain or improve standing balance, gait, general function and community integration post stroke will be assessed with the following tests:Berg Balance Scale (BBS) [21]. The BBS tests balance and mobility using 14 items scored from 0 to 4.Timed Up And Go (TUG) [22–24]. The TUG assesses the time required to stand up, walk 3 m, return and sit down. There are 3 versions, original, manual (performed while holding a cup of water) and cognitive (performed while also doing a cognitive task).Five Times Sit-To-Stand Test (FTSST) [25]. The FTSST tests the time it takes to stand up from a chair and sit down again five times.Community Balance and Mobility Scale (CB&M) [26]. The CB&M assesses more difficult balance tasks that are relevant to community ambulation.Quantitative analysis of quiet stance and limits of stability in standing [27]. These tests provide quantitative information about the neural mechanisms of postural control [1].Stroke Impact Scale (SIS) [28]. The SIS assesses health status after stroke.Reintegration to Normal Living Index (RNLI) [29]. The RNLI assesses the degree to which individuals have reintegrated back into normal social activities after illness. It has acceptable reliability and validity.

All of these scales have adequate to excellent reliability, validity and responsiveness to change (except responsiveness to change for the FTSST) [26, 28, 30–36].The Motivation for Physical Activity Questionnaire will be administered before the VRT protocol only, to better describe the participant sample [37].3.The results of the BBS will be assessed and used to calculate an effect size in order to estimate the sample size for a definitive RCT.

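### Complete-case ANOVA leaves out randomized participants with no 6-week score and people who become unable to do the timed tests; the resulting bias can go either way

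*Protocol article*

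**What the plan says.** The missing-data rule under Data management and analysis is explicit: "Missing data will be handled using complete case analysis". It stands beside a pre/post ANOVA for each scale measured twice ("within-group factor, time; between-group factor, group; interaction, time x group").

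Under Outcome measures, loss is a feasibility outcome with a trigger: "Retention of participants will be measured and a loss of more than 25% will suggest that changes should be made to the protocol". The trigger is not split by arm. The same section defines the timed tests as times, for example "The FTSST tests the time it takes to stand up from a chair and sit down again five times", and gives no value for a person who cannot do one. It takes the effect size for the definitive sample size from the BBS, whose 14 items are each scored 0 to 4.

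Sample size and recruitment gives the number: "The sample size of two groups of 20 is based on available time and recruitment expectations and funding level". The Trial Registration paragraph reports an amendment "to decrease enrollment from 40 to 20 due to a cut in study funding" and recruitment difficulty. Introduction and objectives makes the comparison of physical outcomes a secondary objective, framed as the potential to maintain or improve them.

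**The concern.** Complete-case analysis is a stated rule here, not a detail left to a later document. Two groups leave the comparison.

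- **No 6-week score.** A randomized participant with only a baseline contributes nothing to the time-by-group term. The post-assessment requires a return to hospital, so a person who has declined may be less likely to attend.
- **Unable at 6 weeks.** Entry requires 2 minutes of independent standing, while the battery includes walking and repeated chair rises. Someone who could do TUG or FTSST at baseline and cannot at 6 weeks has deteriorated in the most informative way, yet drops out of that test's analysis.

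At stake are the answer to the maintain-or-improve question and the BBS effect size carried to the definitive trial. The Discussion also says the results will inform the choice of outcome measures for that trial, so TUG and FTSST results from those still able to do them may influence that choice.

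**Working it through.** **No figure to reproduce.** The article says "No sample size calculation was performed as this is a feasibility trial". Its own inputs are the complete-case rule, the 2 × 2 ANOVA, the 1:1 allocation, the 25% retention trigger, and N = 40 (20 on the amended registration). The rest is assumed: normal change scores with SD 1, a true standardized effect of 0 or 0.50, the split of loss by arm, two-sided alpha 0.05 and power 80%.

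**Step 1: what is estimated.** With two time points and complete cases, the time-by-group term is the difference between arms in mean change among completers. At 25% loss, 30 of 40 remain, or 15 of 20.

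**Step 2: shift within one arm.** If the worst fraction p is lost, the completers' mean rises by k(p) = φ(z_p)/(1 − p).
- k(0.25) = 0.3178/0.75 = 0.424
- k(0.10) = 0.1755/0.90 = 0.195

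**Step 3: bias between arms.** Raw bias = k(p_VRT) − k(p_control).
- 25% VRT, 10% control: 0.424 − 0.195 = +0.23 SD
- 10% VRT, 25% control: −0.23 SD
- Equal loss: 0

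If loss is only moderately related to outcome (latent correlation 0.5), these halve to +0.11 and −0.11 SD.

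**Step 4: shrinkage of the SD.** Variance after losing the worst 25% is 1 + z·k − k² = 1 − 0.286 − 0.180 = 0.534, so the SD is 0.73. With equal loss, the raw difference of 0.50 is unbiased, but standardized by the completers' SD it is 0.50/0.731 = 0.68. With correlation 0.5, the variance is 1 − 0.25 × (1 − 0.534) = 0.88, the SD is 0.94, and the effect is 0.53.

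**Step 5: effect on the definitive sample size.** n per arm = 2(1.960 + 0.842)²/d² = 15.70/d². An effect of 0.50 needs 63, 0.53 needs 56 and 0.68 needs 34.

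| Loss, VRT / control (true effect 0.50) | Raw difference | Standardized | n per arm |
|---|---|---|---|
| Random | 0.50 | 0.50 | 63 |
| Worst 25% / worst 25% | 0.50 | 0.68 | 34 |
| Worst 25% / worst 10% | 0.73 | 0.92 | 19 |
| Worst 10% / worst 25% | 0.27 | 0.34 | 133 |
| Same cut-off in both arms (12% / 25%) | 0.30 | 0.39 | 104 |

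The last row matters for direction. If VRT works and the same poor result leads to loss in either arm, control loses more people and the effect is understated.

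**Step 6: precision.** The approximate 95% half-width of the standardized difference is t × √(2/n): 0.75 with 15 per arm, and 1.12 with an average of 7.5 per arm.

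**The case against.** A reader might infer that the rule biases the VRT effect upward. The documents do not support that. Dropping poor performers raises each arm's own mean; the difference rises only if VRT loses more of them. The article gives no loss by arm and no link between loss and outcome. Its active control and equalized contact work against imbalance, although the two arms carry different burdens and participants know their arm. The outcome assessor is blinded.

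A reader might also take 0.42 SD as the size of the bias. That is one arm's shift under perfect selection on change with no control loss. If loss depends on the 6-week score instead, with equal SDs and an assumed pre-post correlation r, the shift in mean change is (1 − r) × 0.424 score SDs: 0.13 at r = 0.7 and 0.08 at r = 0.8. If loss depends on a low baseline, the shift is equally large but downward.

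Third, inability on TUG or FTSST does not reach the definitive sample size. That rests on the BBS, where poor performance can be scored. Only a missed assessment affects it.

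Finally, efficacy is secondary, retention and completion are reported, the article admits limited ability to detect differences, and sampling error exceeds every raw bias computed here. All of this stands and limits the weight of the point. It does not remove it: a confidence interval does not cover selection bias, and reporting retention does not correct it. The article's rule on inability to complete measures is a contingency, not a forecast, and nothing in it says that people who stop exercising are not assessed.

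**Conclusion.** The point holds as a weakness in a stated rule, with direction unknown. Complete-case ANOVA omits randomized participants without a 6-week score and leaves deterioration to inability uncounted on TUG and FTSST, so those results describe only people able to do the test.

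Under the illustrative assumptions, the raw between-arm bias runs from about −0.23 to +0.23 SD for a 25%/10% split of the worst cases, and is zero with equal or random loss. The one upward route that needs no imbalance is SD shrinkage, which applies only to a non-zero standardized effect: 0.50 becomes 0.53 to 0.68 at 25% loss, and the planned n falls from 63 to between 56 and 34 per arm. The split, the strength of selection, the effect, alpha and power are all assumptions; only the 25% trigger comes from the article. The conclusions on recruitment, retention and safety are untouched.

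**What to change.** - **Main analysis.** Replace the complete-case ANOVA with an analysis of all randomized participants in their allocated arm: a likelihood-based longitudinal model with baseline means constrained equal across arms. Baseline-only participants then contribute. This removes bias from loss related to baseline, but not from loss related to the unseen 6-week outcome, so the next two items are also needed.
- **Timed tests.** Record 'attempted but unable' separately from 'not assessed', and give the former a value. One option is to analyse TUG and FTSST as speed (1/time) with unable set to 0, and to report seconds alongside.
- **BBS sensitivity analysis.** Vary the assumed outcome of missing participants in both arms, including unequal assumptions. Changing the VRT arm alone would be one-sided.

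The cost is one extra code on the assessment form, slightly more analysis work, and timed tests reported on two scales. Sample size and visits do not change.

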**Methods:**

Forty patients who can stand for at least 2 min and are soon to be discharged from inpatient or outpatient rehabilitation post stroke are being recruited in Ottawa, Canada and being randomized to control and experimental groups. Participants in the experimental group use home-based VRT to do rehabilitative exercises for standing balance, stepping, reaching, strengthening and gentle aerobic fitness. Control group participants use an iPad with apps selected to rehabilitate cognition, hand fine motor skills and visual tracking/scanning. Both groups are instructed to perform 30 min of exercise 5 days a week for 6 weeks. VRT intensity and difficulty are monitored and adjusted remotely. Weekly telephone contact is made with all participants. Ability to recruit participants, ability to handle the technology and learn the activities, compliance, safety, enjoyment, perceived efficacy and cost of program delivery will be assessed. A battery of assessments of standing balance, gait and community integration will be assessed for feasibility of completion within this population and potential for improvement following the intervention. Effect sizes will be calculated.

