### Procedures and participant timeline

Participants in both groups (and their study partners) attend a total of 4 sessions at Élisabeth Bruyère Hospital (see Fig. 2). The first 3 sessions occur a week or two before discharge from inpatient or outpatient rehabilitation. At sessions 1 and 2, each lasting 45–60 min, participants and their study partners are trained on how to use the VRT system or iPad and how to play the games. They are also instructed what to do if something goes wrong (for example, if the participant falls or the equipment did not work). Participants are given an instruction manual. Pre-outcome measures are performed by the RA at a third session, lasting approximately 1½ h.

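### The two-time-point mixed ANOVA compares raw change between arms; adjusting for the baseline already collected would protect against chance imbalance and usually be more precise

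*Protocol article*

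**What the plan says.** Under Data management and analysis, each scale except the PACES (measured only after the intervention) "will be compared using mixed-methods analysis of variance (ANOVA) (within-group factor, time; between-group factor, group; interaction, time x group"). For the ellipse measures from quiet stance and limits of stability, "Results will be compared over time using mixed-methods ANOVA as aforementioned". No baseline covariate is named. Scale scores "will be reported as mean (95% confidence intervals"), before and after the intervention.

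There are two assessments. Under Procedures and participant timeline, "Pre-outcome measures are performed by the RA at a third session"; after the six-week programme, "the physical outcome measures and community integration questionnaires are repeated".

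The between-group result has a later use. The Abstract (Methods) says "Effect sizes will be calculated", and Outcome measures says that the BBS results will be "used to calculate an effect size in order to estimate the sample size for a definitive RCT".

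On size, Sample size and recruitment states "The sample size of two groups of 20 is based on available time and recruitment expectations and funding level". The Trial Registration paragraph of the Abstract records a reduction in enrolment from 40 to 20. Both sizes are used below.

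**The concern.** A repeated-measures ANOVA with only two occasions looks richer than it is. Of its three tests, only the interaction compares the arms on what happened after the intervention began, and it does so by subtracting the whole baseline score. The group main effect averages the pre and post scores, so in expectation it holds only half of any effect on the post score. The time main effect pools both arms and includes natural recovery, which the Introduction leads one to expect in patients recently discharged from inpatient rehabilitation.

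Subtracting the whole baseline over-corrects whenever the slope of post on pre (correlation x SD post / SD pre) is below 1. An arm that starts higher by chance then tends to show less gain, and the reverse. Randomization is described as permuted blocks, with no stratification on function mentioned, so nothing in the described design limits such imbalance in 10 to 20 people per arm.

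At stake are the comparison with the iPad arm in the second secondary objective and the BBS effect size that is to set the size of the definitive trial.

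**Working it through.** The protocol states no power or precision figure, so there is none to reproduce.

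**Inputs.** From the article: one pre and one post score, two arms, 1:1 allocation, N = 40 or 20. Assumed: pre-post correlation ρ of 0.5, 0.7 and 0.9, and equal pre and post SDs (set to 1). The documents give neither quantity.

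**1. The interaction is a change-score test.** On a simulated data set with 20 per arm, the time x group F was 1.3527 and the squared two-sample t on change scores was 1.3527. The identity is algebraic, so it holds for any data with two occasions.

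**2. How likely is imbalance?** The SD of the difference in baseline means is √(2/n): √(2/20) = 0.32 SD at 20 per arm and √(2/10) = 0.45 SD at 10 per arm. In 20,000 simulated trials per setting, a difference beyond 0.3 SD in either direction arose in about 34% at N=40 and 50% at N=20.

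**3. What does imbalance do?** With no true effect and a baseline difference d, the change-score estimate has expectation −(1−ρ)d. For d = 0.3:
- ρ = 0.5: −0.5 x 0.3 = −0.15 SD
- ρ = 0.7: −0.3 x 0.3 = −0.09 SD
- ρ = 0.9: −0.1 x 0.3 = −0.03 SD

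Simulated trials with d between 0.25 and 0.35 agreed (−0.153, −0.081, −0.026 at N=40; −0.143, −0.095, −0.027 at N=20). The ANCOVA estimates in the same trials averaged within 0.01 SD of zero.

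**4. Precision.** In units of 2s²/n, the variance of the difference is 2(1−ρ) for change and 1−ρ² for ANCOVA, a ratio of (1+ρ)/2. Estimating the slope multiplies this by 1 + 1/(N−4), which is 1.028 at N=40 and 1.0625 at N=20. The CI ratio also allows for the lost degree of freedom.

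| ρ | Large sample | N=40 variance (CI width) | N=20 variance (CI width) |
|---|---|---|---|
| 0.5 | 0.75 | 0.77 (0.88) | 0.80 (0.90) |
| 0.7 | 0.85 | 0.87 (0.94) | 0.90 (0.95) |
| 0.9 | 0.95 | 0.98 (0.99) | 1.01 (1.01) |

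Simulated variance ratios were 0.77, 0.88, 0.98 and 0.80, 0.90, 1.01. The variances are equal at ρ = 2/[1 + 1/(N−4)] − 1, which is 0.95 at N=40 and 0.88 at N=20. If a quarter of participants were lost, the loss at which the article would revisit its protocol, the break-even falls to 0.93 (N=30) and 0.83 (N=15).

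**5. Why the SD basis matters.** As an illustration, take a definitive trial with an assumed difference of 0.5 SD on the post score, two-sided 5% and 80% power. Then n per arm = 2(1.96+0.84)²V/0.5², where V is 1 for the post score alone, 2(1−ρ) for change and 1−ρ² for ANCOVA.

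| ρ | Post score alone | Change | ANCOVA |
|---|---|---|---|
| 0.5 | 63 | 63 | 48 |
| 0.7 | 63 | 38 | 33 |
| 0.9 | 63 | 13 | 12 |

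**The case against.** The change-score test is valid and unbiased over randomization; the bias in step 3 is conditional on an observed imbalance. Nor are imprecision and imbalance two separate harms. The excess variance of change over ANCOVA is 2(1−ρ) − (1−ρ²) = (1−ρ)², which is exactly the imbalance component. All of this stands.

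The gain also depends on a correlation that the documents do not give. At ρ = 0.9 it is negligible at N=40 and slightly negative at N=20. Even at ρ = 0.5, the mean CI width at N=20 falls only from 1.85 to 1.66 SD, and neither is narrow enough to fix an effect size well. The outcomes are secondary, the feasibility thresholds do not use the ANOVA, no power is claimed, and the Discussion concedes limited ability to detect differences. This limits the weight of the point but is no reason to prefer raw change.

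The baseline itself is imperfect: it is taken after two training sessions on the assigned system. If those sessions already shift scores, change scores subtract that shift in full and ANCOVA only in proportion to the slope, so this does not favour the ANOVA.

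A reader might infer that only per-arm means will be reported, or that a between-group interval will never appear. The text does not support this: effect sizes are planned in the Abstract and for the BBS, and an article's silence on the interval does not rule it out. A reader might also infer that the wrong SD will be carried into the definitive trial. The article does not say which SD it will use, so the basis is undefined and cannot be called wrong. Finally, the article lists the main effects as model terms and nowhere calls them treatment effects.

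**Conclusion.** The point holds as a modest, nearly free improvement to the analysis of secondary outcomes. The stated comparison is an unadjusted change-score test. At the planned or reduced size, a baseline difference beyond 0.3 SD is expected in roughly a third to a half of trials for any one outcome, and it would move the estimate by about 0.03 to 0.15 SD over the correlations considered. ANCOVA removes that shift. It cuts variance by about 20 to 23% at ρ = 0.5 and 10 to 13% at ρ = 0.7, with essentially no gain at ρ = 0.9.

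These sizes rest on assumed correlations and equal pre and post SDs. It would be too strong to say that the planned test is invalid or that ANCOVA is always more precise. The point matters chiefly because the BBS effect size is to set the size of the definitive trial.

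**What to change.** For each scale and ellipse measure taken before and after, regress the post score on group and baseline score, and report the adjusted between-group difference with its 95% CI as the main comparison. For the BBS, base the effect size on this estimate, and report the residual SD and the pre-post correlation so that the definitive trial can be sized for the analysis it will use. Keep per-arm pre and post means as description, and do not read the group or time main effects as treatment effects.

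The cost is a change of wording, one degree of freedom, and a negligible loss of precision if the correlation proves very high. No extra data or visits are needed.

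### PACES, an enjoyment score taken only after treatment at the outcome visit, should not serve as a motivation variable that explains the physical outcomes

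*Protocol article*

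**What the plan says.** Under Data management and analysis, linear regression is to determine "what proportion of the results of the physical outcome measures is explained by motivation to undertake physical activity", with motivation "assessed with the Motivation for Physical Activity Questionnaire and the PACES". This fixes both explanatory variables and the interpretation.

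The two measures differ in timing and purpose:

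- **PACES.** Outcome measures introduces it, under the acceptability objective, as the "Physical Activity Enjoyment Scale, which rates (from 1 to 7) 18 statements of one’s feelings about physical activity", and says it is "administered at the post hoc assessment only". Data management and analysis confirms the timing when it leaves the scale out of the pre/post comparison ("except the PACES, which is assessed post-intervention only"). Procedures and participant timeline puts it at the post-intervention visit, where "the physical outcome measures and community integration questionnaires are repeated, the PACES is administered".
- **Motivation for Physical Activity Questionnaire.** According to Outcome measures it "will be administered before the VRT protocol only, to better describe the participant sample".

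The article does not say whether the proportion explained is raw or adjusted R-squared, whether the model contains group or baseline score, or whether it is fitted in both arms together.

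**The concern.** To say that motivation explains an outcome, the motivation score should come before the outcome and should not be produced by the treatment. PACES meets neither condition securely.

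1. **Order in time.** PACES and the post-treatment physical tests come from the same visit. A participant who has improved may report more enjoyment of physical activity. Nothing in the design separates that from enjoyment leading to improvement.
2. **Construct.** The same score is an acceptability result of VRT in one section and a measure of motivation in another.
3. **Arm as a common cause.** VRT is physical exercise. The iPad program is not, and the Introduction and objectives section says the apps were not expected to affect the physical outcomes. The Discussion expects participants to enjoy VRT and hypothesizes that it may improve function. If both hold, a model that pools the arms could show a PACES-outcome association with no role for motivation.

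At stake is a published share of outcome attributed to motivation that could be partly a consequence of improvement or of allocation.

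**Working it through.** The article gives no R-squared, power or sample-size figure to reproduce. Two checks follow.

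**Inputs from the protocol article**
- Predictors: k = 2 (Data management and analysis).
- Planned n = 40, two groups of 20 (Sample size and recruitment).
- Amended n = 20 (Abstract, Trial Registration).
- Complete-case analysis, so n can only fall (Data management and analysis).

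**Check 1: chance alone, if unadjusted R-squared is reported (an assumption)**

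With no true relation, R-squared follows Beta(k/2, (n − k − 1)/2), which for k = 2 is Beta(1, (n − 3)/2).
- Mean = k/(n − 1) = 2/(n − 1).
- 95th percentile = 1 − 0.05^(2/(n − 3)).
- P(R-squared ≥ 10%) = 0.9^((n − 3)/2).

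| n | Mean | 95th percentile | P(R-squared ≥ 10%) |
|---|---|---|---|
| 40 | 2/39 = 5.1% | 1 − 0.05^(2/37) = 15.0% | 0.9^18.5 = 14% |
| 20 | 2/19 = 10.5% | 1 − 0.05^(2/17) = 29.7% | 0.9^8.5 = 41% |

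Adjusted R-squared, 1 − (1 − R²)(n − 1)/(n − 3), has a mean of about 0 under the same null at both sizes. It removes this part.

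**Check 2: reverse causation only**

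In 10,000 simulated data sets per setting, the motivation questionnaire had no relation to outcome, and PACES was generated from the outcome with correlation r. The values r = 0.3 and 0.5 are assumptions; the documents give none.

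| r | n | Mean raw R-squared | Mean adjusted R-squared | Overall F test p < 0.05 |
|---|---|---|---|---|
| 0.3 | 20 | 18% | 8% | 19% |
| 0.3 | 40 | 13% | 9% | 37% |
| 0.5 | 20 | 31% | 23% | 52% |
| 0.5 | 40 | 28% | 24% | 86% |

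Adjusted R-squared stays close to r² (0.3² = 9%, 0.5² = 25%). It estimates the association correctly, but in these data none of that association is motivation acting on outcome. A larger sample does not help: the artefact remains and reaches significance more often.

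The documents give neither the size nor the direction of any arm effect on PACES, so no figure is put on the common-cause route.

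**The case against.** The strongest reply is that one sentence in a condensed article states an aim and does not specify a model. The type of R-squared, the covariates and the analysis population are commonly left to a fuller plan. That stands: the absence of group and baseline score from the sentence is no finding, and the chance figures apply only if raw R-squared is used.

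A reader might also infer something stronger, namely that the regression is bound to report motivation effects that are noise or reverse-caused, with an error that is always upward. The documents do not support this:

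- Raw R-squared is nowhere stated. Even if it were used, its upward bias holds on average and not for every estimate.
- The most striking chance figure, a mean of 2/9 = 22% at n = 10, needs a fit within one arm after the cut to 20. No such restriction is stated. It also cannot be combined with the arm argument, which needs the arms pooled.
- The motivation questionnaire precedes the intervention, so post-treatment improvement cannot have caused its score.
- A real relation between motivation and outcome is not excluded.
- An arm effect on PACES is plausible but assumed. The scale concerns physical activity in general, and both arms are encouraged to walk and to join exercise groups and therapy.

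Finally, the regression answers no numbered objective and feeds none of the feasibility thresholds, and the BBS is the basis for the future sample size. The Discussion's list of what will inform the definitive trial names neither motivation nor participant selection. This limits the consequence. It does not answer the timing and construct problem, which the article itself fixes.

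**Conclusion.** The point holds for PACES. An enjoyment score taken only after treatment, at the outcome visit, and used elsewhere as an acceptability outcome cannot support a statement that motivation explains the physical results. This rests on the article's own text and needs no numerical assumption.

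The size of the distortion is uncertain. The chance part is modest at n = 40 and larger at n = 20, and it exists only if R-squared is unadjusted. The reverse-causation part depends on an unknown correlation and survives adjustment of R-squared. The baseline questionnaire does not share that problem.

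The point is minor: it affects the interpretation of an exploratory analysis and leaves the feasibility conclusions untouched.

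**What to change.** - Use only the baseline Motivation for Physical Activity Questionnaire as the explanatory variable.
- Model the post-intervention score on baseline score, group and motivation.
- Report the motivation coefficient with its 95% confidence interval, and an adjusted or partial R-squared. An unadjusted partial R-squared still has a null mean of 1/(n − 3) in this model (1/37 = 2.7% at n = 40, 1/17 = 5.9% at n = 20), so it should be read beside the interval.
- Keep PACES as a post-treatment acceptability outcome, summarized by arm. The planned mean with 95% confidence interval already serves most of this. Describe any PACES-outcome relation as an association only.

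The cost is a change of analysis wording, with no new data or visits. The exploratory regression loses one predictor.
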